### Sample Size Calculation and Feasibility of Recruitment

The sample size was calculated to detect a clinically important difference of 3.5 points in mean change from baseline to 6 months in the primary outcome measure, severity of depressive symptoms, using the Centre for Epidemiological Studies in Depression (CES-D) Scale [87]. In the general population, a difference of this size would be associated with increased risk of functional decline, stroke, myocardial infarction and mortality [88,89]. Using a standard deviation of 9.0 as a conservative estimate and a difference of -3.5 points, a base sample size of 105 was estimated to be sufficient to address this primary outcome (two-tailed alpha = 0.05; beta = 0.20).

Our primary analysis of the factors that predict the severity of depressive symptoms will be addressed using regression analysis with the change (6-month-baseline) in the CES-D score as the dependent variable. The predictor variable: dose of the intervention (low, moderate, high), and potential confounding variables representing known risk factors for depression (female gender; prior history of depression; antidepressant medication use; living alone; cognitive impairment; family caregiver with depression; widowed, divorced or separated; low income (< $40,000 per annum); co-morbid health conditions; hospital admission in last 6 months; age; use of three or more prescription medications; presence of anxiety disorder; low social support; poor health-related quality of life; excessive consumption of alcohol; taking depressogenic medications; recent stressful life event; presence of risk factors for cardiovascular disease; and chronic pain) [17], will be included in the initial models. Norman & Streiner [90] recommend 5 participants for each independent variable included in a regression model; therefore, since the study included twenty independent confounding variables, and taking into account a possible 20% attrition rate, the minimum sample size was calculated as follows: 105 + (5 × 20) = 205 plus 20% = 246. In order to ensure a case to variable ratio that would suffice the number of variables, an even larger sample of 250 participants was planned for recruitment. The estimated attrition rate was based on an earlier trial in which 84% of the study participants completed the 6-month follow-up [70].

Our previous pilot study in the HNHB CCAC found that, on average, 100 long-stay (> 60 days) home care clients, 70 years or older, are referred to the CCAC for PSS [Unpublished Report, [name], 2007]. Based on our previous trials with this population, it is expected that approximately 30% will screen positive for depressive symptoms [70,78,91] and meet all eligibility criteria, and 10 (33%) of these eligible clients will refuse to consent for the study. Thus, we predicted that it would be possible to prospectively recruit 250 older adults with depressive symptoms in thirteen months (20 per month). Recruitment began in May 2010 and is expected to be completed in June 2011 (13 months).

### Intervention

The nurse-led intervention consists of standard home care services plus home visitation by a designated team of RNs and a PSWs a minimum of once per month over a 6-month period. Standard home care services include routine follow-up by the CCAC case manager whose focus is on assessing the client's eligibility for in-home health services, arranging and coordinating professional (e.g., nursing, occupational therapy, physiotherapy, social work, speech-language pathology, and dietitian) and non-professional PSS, providing information and referral to community agencies, and monitoring and evaluating the plan of care on an ongoing basis through in-home assessments. The CCAC care coordinator determines eligibility and priority level for home care services and the amount and type of home care services required, based on set criteria [21].

The designated RN and PSW team provides a comprehensive, collaborative and evidence-based approach to the prevention, recognition and management of depression through regular home visits, standardized screening protocols, modification of risk factors for depression, depression education, support of antidepressant medication management, referral and linkage to health and social services, delivery of PST and social and behavioural activation, monthly case conferencing, and the development of a single, evidence-based depression management plan. The intervention, which is individualized to the client's needs, is coordinated by the RN. The RN provides leadership and coordinates communication between the client and their family caregiver, the PSW, the CCAC CM, the client's primary care physician (PCP), and other IP providers. The aim of the designated team of RNs and PSWs is to recognize, manage, and reduce the severity of depressive symptoms to enhance health-related quality of life (HRQOL) and reduce on-demand use of expensive health services. The frequency and timing of the home visits and case conferences is based on individual client needs and the results of the ongoing assessment of the client's progress toward the goals.

At each home visit, the RN systematically assesses for depression risk factors using the depression risk management protocol (Table 1), and monitors responsiveness to treatment using the Geriatric Depression Scale-15 (GDS-15) [92]. The RN supports antidepressant medication management in collaboration with clients and their PCP using evidence-based guidelines [17,18]. During the initial treatment period, when starting or modifying antidepressants, the RN conducts weekly telephone reassessment for at least four weeks to assess response, side effects and to titrate the dose [17]. Following initial improvement (< 6 on the GDS-15) [92], ongoing follow-up through monthly home visits is provided to assess clinical outcomes and support adherence to treatment [17]. For clients who do not respond to initial treatment (≥ 50% reduction in depressive symptoms is not achieved) treatment is discussed with the client's PCP [17,18]. At each visit, the PSW also monitors depressive symptoms using the behavioural rating scale for intramural psychogeriatric inpatients (GIP-28) [93]. The PSWs are expected to keep detailed records and report their observations and concerns to the RN. Two RCTs have demonstrated that use of the GIP-28 by PSWs working in collaboration with an RN is an effective, feasible, and acceptable strategy for increasing the recognition of depressive symptoms in older adults [71,72]. Clients and their caregivers also receive education on depression using printed educational materials (from the Canadian Coalition for Seniors' Mental Health and Canadian Mental Health Association).

Each client's treatment regimen is discussed by the RN and PSW at a case conference held a minimum of once per month for 6 months. A depression care booklet is used to systematically guide the RN and PSW team through a series of questions that triggers assessment of depressive symptoms, current treatment, treatment response, risk factors for depression [17,18,57,58,82,83], use of social and behavioural activation and PST, and recommended actions for reducing depressive symptoms and promoting health-related quality of life.

The RN assesses client's problem-solving strengths and limitations using the Problem-Solving test, and provides a minimum of 6 sessions of PST using Nezu et al.'s [84] manual, as part of their home visit. PST consists of teaching participants a five-step problem-solving model. The overall goal of PST is to help the depressed person develop skills in order to approach life problems in an active fashion, using the steps of problem-solving as a coping strategy [17,84]. A series of RCTs conducted in primary health care and other community settings have demonstrated that PST provided by RNs is an effective, feasible, and acceptable treatment for depression in older adults [40,41,46,49,94,95]. We selected Nezu et al.'s [84] problem-solving method because of its sequenced approach to teaching problem-solving and its emphasis on problem orientation, a critical element of problem-solving therapy [96].

In our application, we use the therapy's five steps which consist of: a) developing a positive, optimistic attitude toward the problem and one's ability to cope with it; b) defining the problem and setting realistic goals; c) discussing and evaluating different ways to reach goals; d) creating action plans; and e) evaluating their effectiveness in reaching goals [84]. However, the RN is more directive than specified in the original PST instructions, and participants are encouraged to focus on less complex problems to facilitate learning. During the initial home visits, clients are asked to identify the most frequent or stressful problems they are encountering and how they are managing the problem. The RN then assists the client to effectively apply the problem-solving steps to address each problem in a sequential order as prioritized by the client using a problem-solving worksheet.

Social and behavioural activation involves assisting and encouraging clients to participate in a regular physical activity program that is tailored to individual needs by providing information, personal counselling, support, and skills training to overcome barriers to increasing their physical activity levels. Physical activity is encouraged through the use of the Home Support Exercise Program (HSEP) [85]. The RN introduces the client to the program, assesses their interest and ability, and authorizes the PSW to start the client on the program. Using one-on-one coaching, the PSW and client begin working through the ten exercises and seven healthy eating tips with the client, along with the HSEP resources and a progress chart [85]. The goal of social and behavioural activation is to increase client and caregivers' interactions outside the home by facilitating referrals to seniors' programs, support groups or other community services [49].

The RN develops an evidence-based plan of care to meet mutually agreed upon and attainable goals in collaboration with the client and caregiver, the PSW, the client's PCP, and the other members of the IP team. The plan includes specific short-term and 6-month goals, a list of actions and referrals and a record of all recommendations. The results of the initial and ongoing assessment, and the client's response to treatment, are documented in the care plan and reviewed during each case conference. This includes documenting the client's level of adherence to the recommendations and reasons for non-adherence. The RN liaises with the client's PCP and other providers to initiate referrals to a comprehensive range of services and supports to address individual client needs. The RN alerts the PCP to the presence of depression, dementia, delirium using a standard letter, which is sent directly to the PCP requesting further assessment and treatment (Figure 2).

**Figure 2 F2:**
[figure not shown]
**Graphical Depiction of Intervention and Measurements**. Squares represent fixed elements. Circles represent activities that are flexible. Measurements are bolded. This graphical method was proposed by Perera et al. [134].

### Outcome Evaluation

The aim of the outcome evaluation is to examine the effect of the IP mental health promotion intervention on clinical outcomes among the target population.

#### Data Analyses

Quantitative data will be cleaned, checked for out of range values, skip pattern problems and duplicates. Tests of normality will be completed to determine appropriateness of statistical methods. All analyses will be performed using the Statistical Package for the Social Sciences (SPSS) version 19.0 for Windows on an intention-to-treat basis. All statistical tests will be performed using two-sided tests at the 0.05 level of significance. For all models, the results will be expressed as effect (or odds ratio for binary outcomes), standard errors, corresponding two-sided 95% confidence intervals (CI), and associated p-values. Descriptive analysis of demographic characteristics will be expressed as a mean (standard deviation [SD]) or median (minimum-maximum) for continuous variables and count (percent) for categorical variables.

The primary analysis to address the main outcome measure (change in mean scores from baseline to 6-months in the severity of depressive symptoms) will be tested using analysis of covariance (with pre-intervention scores as covariates). The factors that predict the severity of depressive symptoms will be addressed using regression analysis with the change (6-month-baseline) in the CES-D score as the dependent variable. The predictor variable dose of the intervention (low, moderate, high), and potential confounding variables representing known risk factors for depression, will be included in the initial models. Model assumptions and goodness-of-fit will be assessed by examining the residuals for model assumptions and chi-squared test of goodness-of-fit or qqplots and Hosmer-Lemeshov tests for logistic regression models. We will assess multicollinearity by investigating associations among the confounding variables. For linear models, we will use the variate inflation factor (VIF) to assess collinearity. Variables having a VIF greater than 10 will be considered collinear and will be excluded from the analysis [110]. The secondary hypothesis of change in the prevalence of depressive symptoms, anxiety, HRQOL, cognitive impairment, and the rate of depression treatment from baseline to 6 and 12 months, will be tested using multiple regression (or logistic regression for binary outcomes) using the same approach as in the primary analysis. The possibility of co-interventions occurring such as mental health-related counselling and support programs will also be monitored.

We will also perform the following sensitivity analyses which will involve: a) use of multiple imputation to handle missing data, b) analysis of all outcomes analysed simultaneously using multivariate analysis of covariance (MANCOVA) to account for correlation among them, c) longitudinal analysis of data using generalized estimating equations (GEE) to account for the serial correlation of all outcomes at baseline, 6 and 12 months within a subject, and d) clustering among individuals who live together. The GEE is a technique that specifies the correlation structure between participants [111]. This approach produces unbiased estimates under the assumption that missing observations will be missing at random. An amended approach of weighted GEE will be employed if missingness is found not to be at random [111]. We will assume an autoregressive AR(1) correlation structure for the GEE analysis, which assumes that serial responses measured closer to each other are more correlated than those that are far apart.

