#### Variables and Measures

Assessment of the *feasibility of the intervention *will include: a) the reach of the intervention, defined as the proportion of the intended target population that actually participated in the intervention, b) the dose delivered, defined as the number and duration of the home visits and case conferences during the 6-month intervention, and c) the level of fidelity to treatment (the extent to which the RNs and PSWs adhere to the components of the intervention). We are keeping a record of all clients who meet the eligibility criteria for the study to determine the recruitment rate and assess the reach of the intervention. Alphanumeric characteristics (age, gender, medical diagnosis, referral source) of the clients who are assessed as eligible for the study but refuse to participate will be collected at baseline to assess the representativeness of the sample. Data on the dose of the intervention and the RNs' and PSWs' actual adherence to the intervention will be gathered by the RNs and PSWs themselves by means of prospective self-reports. The RNs and PSWs will use the monthly visit and case conference record and the depression care booklet after each case conference to record which components of the intervention were applied. Each item will be scored as a done/not done binary variable (see Table 3 for the key intervention features that will be scored) [122,123].

**Table 3 T3:** Fidelity Scale

Intervention Components	Data Source	Yes	No

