#### Data Analyses

Study participants will be compared with clients who are assessed as eligible for the study but refuse to participate on their alphanumeric characteristics at baseline using independent t-tests for continuous variables and chi square for categorical variables. Descriptive analysis of the dose of the intervention will be expressed as the mean (standard deviation [SD]) and range (minimum-maximum) number of home visits and case conferences. Data on the RNs' and PSWs' actual adherence to the intervention will be categorized as the proportion of times each component of the intervention was implemented. Content analysis of the older home care clients' responses to the open-ended questions will be used to analyse the qualitative data. Participant answers will be sorted into categories and themes. Descriptive analysis will be performed for the frequency of the answers for each question.

The focus groups will be digitally recorded and transcribed verbatim by an experienced transcriptionist and checked for accuracy by a Research Assistant. Qualitative data will be managed using N-VIVO 8 software. Three of the investigators ([name]) will systematically review all transcripts and inductively generate a list of codes by hand describing themes. The codes will be grouped into themes (a higher conceptual level) and sub-themes. The investigators will use a constant comparison approach to interpret data. This will involve reviewing coded data that supported themes and continually referring to previously coded sections for comparison. By comparing and contrasting the coded data, sub-themes, themes, interrelationships and patterns will be revealed. Differences of opinion will be discussed until agreement is reached.

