The second challenge centres on the need to assess the feasibility of the intervention within the local context. It is expected and will be accepted that the intervention protocol may require some adaptation to accommodate client's needs and the unique characteristics of the local context, which will result in variation in the intervention components and dose to which participants are actually exposed [127]. It is therefore important that the processes and outcomes of intervention adaptation be described and systematically evaluated [132]. We are closely monitoring intervention delivery including the components of the intervention that were applied and the dose of the intervention that each participant actually received. Monitoring intervention implementation will provide data on the extent to which the intervention that was received deviates from the intervention as designed [127]. This information will be used to determine the key components and adaptable components of the intervention, thus facilitating future dissemination [132]. In addition, these data will be used to operationalize the intervention in the outcome analysis. That is, the intervention is represented by the actual dose received (number of home visits and case conferences). The outcome analysis consists of examining the relationship between the intervention dose and the level of fidelity to treatment and changes in the outcome scores from pre-test to post-test. This type of analysis accounts for variability in intervention implementation, which increases the statistical power to detect significant effects [133], facilitates a dose-response relationship, and enhances the clinical relevance of the study results [127]. The results will also allow informed speculation on the mechanism through which the intervention improves outcomes.

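### The dose regression uses three bands in the analysis section but a count of visits and conferences in the Discussion; banding a recorded count works against the power and dose-response purpose given for it

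*Protocol article*

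**What the plan says.** The article describes dose in five places, not all in the same form.

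- **Sample Size Calculation and Feasibility of Recruitment**: the regression of 6-month change in CES-D has as predictor "The predictor variable: dose of the intervention (low, moderate, high"), together with a list of possible confounders.
- **Outcome Evaluation, Data Analyses**: "The predictor variable dose of the intervention (low, moderate, high"). This again means three levels.
- **Discussion, second challenge**: in the outcome analysis "the intervention is represented by the actual dose received (number of home visits and case conferences"). The same paragraph says that this kind of analysis raises statistical power and allows dose-response to be examined.
- **Process Evaluation, Variables and Measures**: "the dose delivered, defined as the number and duration of the home visits and case conferences during the 6-month intervention". Duration is now part of the dose.
- **Process Evaluation, Data Analyses**: "Descriptive analysis of the dose of the intervention will be expressed as the mean (standard deviation [SD]) and range (minimum-maximum) number of home visits". This is a numeric summary, and conferences are summarised in the same way.

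Table 2 lists the number and duration of visits and conferences as recorded data. The Intervention section adds that "The frequency and timing of the home visits and case conferences is based on individual client needs".

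**The concern.** Numeric dose data will exist for each participant. The Discussion names the count as what stands for the intervention in the outcome analysis, yet the analysis section puts a three-level version into the model. A reader cannot tell which form is the planned predictor, or whether duration enters at all.

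The choice has consequences. Replacing a count by three bands treats everyone within a band as having had the same exposure. If more contact goes with more improvement in a roughly linear way, that removes usable variation and lowers power, which is the opposite of the reason given for the dose analysis.

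The study has one group and no comparator, so the relation between dose and change is the main quantitative comparison within the study that bears on whether exposure matters. The secondary outcomes are to be analysed by the same approach, so the dose term may carry over to those models as well.

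**Working it through.** **The plan's own figures.** The article gives no power or sample-size figure for the dose regression. Its recruitment arithmetic reproduces: 105 + 5 × 20 = 205; 205 × 1.2 = 246; raised to 250. With 20% attrition, 250 × 0.8 = 200 completers, which is the n used below. Nothing else here depends on the 105.

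**Information kept by banding.** For a linear dose-response, the share kept is the between-band variance of mean dose divided by the total variance of dose.

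Normal dose, equal thirds (assumption): the cut-points are at ±0.4307 SD and the normal density there is 0.3636. The mean of the top third is 0.3636 / (1/3) = 1.091, the bottom third is −1.091 and the middle third is 0. Share kept = (2/3) × 1.091² = 0.793, so 20.7% is lost. This is equivalent to 200 × 0.793 = about 159 participants analysed with the count.

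**Sensitivity to the assumptions.** The article gives neither the distribution of dose nor the band shares.

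| Dose distribution | Band shares (low/moderate/high) | Information lost |
|---|---|---|
| Uniform | equal thirds | about 11% |
| Normal | 27/46/27 | 19% |
| Poisson, mean 12 or 18 | near thirds | about 20% |
| Normal | equal thirds | 21% |
| Normal | 20/60/20 | 22% |
| Normal | 50/30/20 | 24% |
| Negative binomial, mean 12 | near thirds | 27% |
| Exponential | equal thirds | 35% |
| Normal | 10/80/10 | 38% |
| Normal | 80/10/10 | 48% |

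**Power.** Inputs: n = 200, two-sided alpha 0.05 (from the article), and a true dose-change correlation of 0.20, so R² = 0.04 (assumption). Power comes from the noncentral F distribution with noncentrality λ = n × R² / (1 − R²).

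- Count, 1 df: λ = 200 × 0.04 / 0.96 = 8.33; power 82%.
- Equal thirds of a normal dose: R² = 0.793 × 0.04 = 0.0317; λ = 200 × 0.0317 / 0.9683 = 6.55.
  - Bands as a linear trend, 1 df: power 72%.
  - Bands as an unordered factor, 2 df: power 62%.

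Allowing 20 further covariates in the error degrees of freedom changes each power by less than 0.1 percentage points.

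**The opposite case.** Suppose that benefit occurs only in the top third of a normal dose, with the same R² = 0.04 for that step.

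- Linear count: the squared correlation between the step and the dose is 0.3636² / (2/9) = 0.595. R² = 0.595 × 0.04 = 0.0238, λ = 4.88, power 59%.
- Three-level factor: λ = 8.33 on 2 df, power 73%.

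The ranking reverses under a pure threshold.

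**The case against.** The strongest reply is that the texts can be read together: the Discussion says what dose is made of, and the analysis section says how it enters the model, so bands built from the count would satisfy both. The Discussion never says that the count enters as a continuous term, and its remark on power concerns allowing for variable delivery, which graded bands also do to some extent. Dose also has several components once duration is included, and a banded composite is one way to combine them. This softens the conflict to an ambiguity but does not remove it: the article still does not say which form is the predictor, and bands still serve the stated purpose less well when the relation is roughly linear.

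Three further objections stand and limit the point.

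- **The size is conditional.** A reader might take a loss of one fifth as a property of the plan. It depends on an assumed distribution and assumed band shares. About half of the drop from 82% to 62% comes from spending 2 df, a coding that the article does not specify.
- **The count is not always better.** The threshold case above shows this. The intervention is built around minimum contact (at least monthly visits and at least six problem-solving sessions), so a threshold is possible.
- **Confounding remains.** Visits follow client need, so a more powerful test of the dose association does not make it causal evidence.

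A reader might also infer that, because no cut-points appear, they will be chosen after the outcomes are seen and the type I error will be inflated. Taking the best cut-point pair did raise it to about 22% in one simulation. The document does not support that inference: a journal article may leave cut-offs to the full protocol or analysis plan, and nothing in it suggests a search over cut-points.

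**Conclusion.** The point holds in a limited form. The article describes the dose predictor as three bands in two places and as a count of visits and conferences in a third, with duration added in a fourth, and these need to agree. If the relation is roughly linear, the banded form loses about 20% of the information under near-equal thirds of a normal or Poisson dose, with about 11% to 48% across the scenarios computed. At n = 200 and an assumed correlation of 0.20, power is 82% with the count against 72% or 62% with bands.

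The Sample Size section attaches the word primary to the dose regression, so a reader might infer that the main result is weakened. It is not: the Outcome Evaluation tests the primary pre-post change in CES-D by a separate ANCOVA. What is affected is the dose regression, and the secondary models if they carry the same dose term.

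**What to change.** - Make the Sample Size section, the Outcome Evaluation analysis, the Process Evaluation definition and the Discussion describe the same dose variable.
- Use the recorded number of home visits and case conferences as the numeric predictor, linear, with one non-linearity check stated in advance to pick up a threshold or plateau.
- State how visits and conferences are combined, and whether duration is part of the dose or is analysed separately.
- Keep low, moderate and high for display or as a sensitivity analysis, with the cut-offs and their reason set before outcome data are examined.
- Report the dose result as an association, citing that contact frequency follows client need.

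The cost is a few lines of text and no new data. The downside is small but real: if the true effect is a pure threshold, the linear term has less power than the bands (59% against 73% in the case above). The non-linearity check and the banded sensitivity analysis are there to reveal such a pattern.
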